#### Rationale for objectives and endpoint selection

Despite evidence from retrospective and descriptive studies suggesting long-term benefits for early TEVAR intervention among uTBAD subjects, the underlying unanswered question is whether TEVAR confers a benefit of survival. The two previous RCTs, mentioned above, were underpowered to address this issue. Despite the potential theoretical and procedural advantages of various composite endpoints, it was determined that a trial based on a clearly expressed question with a binary outcome will have the most clinical impact. Similarly, focus on the albeit interesting, but not essential, endpoint of aortic morphological changes and imaging findings, would complicate the pragmatic design of this trial.

### Participant timeline {13}

The schedule of enrolment, interventions, and assessments timeline is depicted schematically in Fig. 1.

**Fig. 1 Fig1:**
[figure not shown]
SPIRIT figure. EQ-5D-5D, EuroQOL-5D-5L; HADS, Hospital and Anxiety Depression Score; SF-12, 12-item Short-Form Health Survey; SMT, standard medical therapy; TEVAR, thoracic endovascular aortic repair; uTBAD, uncomplicated type B aortic dissection

### Sample size {14}

The literature supports an overall estimated 5-year survival for TBAD subjects of approximately 80%, i.e., a 5-year mortality of 20% [33]. The above-mentioned INSTEAD-XL clinical trial identified a reduction in 5-year mortality from 19.3 to 11.1% for those who were randomized to TEVAR, corresponding to a hazard ratio of 0.52 [18]. The estimate was not statistically significant, possibly due to a low sample size.

The primary analysis will be based on the intention to treat principle using the full analysis set and all-cause mortality events as confirmed by the local investigator. The primary objective of the study is to determine the superiority of TEVAR versus SMT in reducing the incidence of all-cause mortality. Assuming a true hazard ratio of 0.52 between TEVAR and SMT, using a two-sided alpha of 5%, 80 subjects with primary endpoint events will provide a statistical power of 80% for the test of all-cause mortality between treatment arms, based on an overall 1:1 allocation between TEVAR and SMT and analyzed with a log-rank test. All Scandinavian countries have registries of vital statistics with a high reliability and almost complete follow-up. Consequently, loss-to-follow-up is expected to be negligible, except for migration, and thus a conservative estimate of loss-to-follow-up is given as 3%.

The study is event-driven. With an estimated annual event rate of 4% for the primary endpoint in the control group and a withdrawal probability of 3%, approximately 550 subjects are estimated to provide the required number of primary events.

In summary, the parameters used for the power calculation are as follows:$$\begin{array}{c}\mathrm{Log}-\mathrm{rank}\;\mathrm{test}\;\mathrm{for}\;\mathrm{comparison}\;\mathrm{of}\;\mathrm{two}\;\mathrm{groups}\\\mathrm{Two}-\mathrm{sided}\;\mathrm{significance}\;\mathrm{level}\;(\mathrm{alpha})=0.05\;(5\%)\\\mathrm{Power}\;(1-\mathrm{Beta})=0.80\;(80\%)\\\mathrm{Hazard}\;\mathrm{ratio}=0.52\\\mathrm{Withdrawal}\;\mathrm{probability}=0.03\;(3\%)\\\mathrm{Inflation}\;\mathrm{factor}\;\mathrm{due}\;\mathrm{to}\;\mathrm{single}\;\mathrm{interim}\;\mathrm{analysis}\;(\mathrm{see}\;\mathrm{below})=1.0071\\\mathrm{Estimated}\;\mathrm{number}\;\mathrm{of}\;\mathrm{events},\;\mathrm i.\mathrm e.\;\mathrm{deaths}=80\\\mathrm{Estimated}\;\mathrm{total}\;\mathrm{sample}\;\mathrm{size}=550\times1.0071=554\\\mathrm{Estimated}\;\mathrm{number}\;\mathrm{in}\;\mathrm{each}\;\mathrm{arm}=225\times1.0071=277\end{array}$$

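### The quoted 5-year mortalities (19.3% v 11.1%) imply a hazard ratio of about 0.55, not the planning value of 0.52; at 0.55, 80 deaths give about 75% power

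*Protocol article*

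**What the plan says.** All the inputs are in the Sample size section {14} of the protocol article. It reports that the extended earlier trial "identified a reduction in 5-year mortality from 19.3 to 11.1% for those who were randomized to TEVAR, corresponding to a hazard ratio of 0.52", cites that trial, and adds that the estimate was not statistically significant. The design sentence then reads "Assuming a true hazard ratio of 0.52 between TEVAR and SMT", at a two-sided 5% level: "80 subjects with primary endpoint events will provide a statistical power of 80" per cent, "based on an overall 1:1 allocation between TEVAR and SMT and analyzed with a log-rank test". The parameter list that follows repeats the hazard ratio of 0.52 and the 80 deaths. It applies an inflation factor of 1.0071 for the single interim analysis and gives 554 patients in total. The per-arm line prints "225\times1.0071=277".

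No other basis for 0.52 is given. The trial is described as event-driven, and the Interim analyses section {21b} places the interim look at half the event target, 40 deaths.

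**The concern.** The text presents 0.52 as what the two mortality percentages correspond to. A log-rank power calculation needs a hazard ratio, and two cumulative mortalities at the same time point convert to one through the logarithms of the survival proportions. Done that way, the answer is not 0.52.

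The event target rests on this number, and the event target fixes both the interim and the final analysis. The article itself criticises the two earlier trials as underpowered for survival. If the effect the sponsor has in mind is the 19.3% to 11.1% difference, the stated power is too favourable.

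**Working it through.** **Inputs.** From Sample size {14}: 5-year mortality 19.3% (medical) and 11.1% (TEVAR); planning hazard ratio 0.52; two-sided alpha 0.05; power 80%; 80 deaths; 1:1 allocation; log-rank test; inflation factor 1.0071. From these, (z for alpha + z for power)² = (1.960 + 0.842)² = 7.849.

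**Step 1: reproduce the plan's figure at 0.52.**
- Freedman: events = 7.849 × [(1 + 0.52)/(1 − 0.52)]² = 78.7, rounded up to 79. Then 79 × 1.0071 = 79.6, i.e. 80.
- Freedman power at 80 deaths: Φ(√80 × 0.48/1.52 − 1.960) = Φ(2.825 − 1.960) = 80.6%.
- Schoenfeld: events = 4 × 7.849/(ln 0.52)² = 73.4, rounded up to 74. Power at 80 deaths is 83.3%.

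The plan's figure therefore reproduces, and it matches the Freedman formula.

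**Step 2: what the two percentages imply.**
- Hazard ratio under proportional hazards: ln(1 − 0.111)/ln(1 − 0.193) = −0.1177/−0.2144 = 0.549.
- Odds ratio: (0.111/0.889)/(0.193/0.807) = 0.1249/0.2392 = 0.522.
- Risk ratio: 0.111/0.193 = 0.575.
- Rounding: letting the percentages range over 19.25–19.35% and 11.05–11.15% moves the hazard ratio only between 0.545 and 0.553. The odds ratio moves between 0.518 and 0.526.
- Reverse check: 19.3% control mortality with a hazard ratio of 0.52 gives 1 − 0.807^0.52 = 10.6%, not 11.1%.

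**Step 3: power with 80 deaths at 0.549.**
- Freedman: Φ(2.606 − 1.960) = 74.1%.
- Schoenfeld: Φ(½ × √80 × |ln 0.549| − 1.960) = Φ(2.684 − 1.960) = 76.6%.
- Simulated log-rank test (554 patients, 3-year uniform accrual, control hazard 0.0446 per year, analysis at the 80th death, no interim look, 20,000 runs): 75.7%. The same simulation at 0.52 gives 81.8%.

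Within one formula the loss is about 6.5 points: 80.6% to 74.1%, or 83.3% to 76.6%.

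**Step 4: deaths needed for 80% power at 0.549.** Freedman 92.4, so 93; Schoenfeld 87.2, so 88. The 1.0071 factor adds about one death to each.

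**Step 5: can 554 patients supply them?** The article gives a 4% annual control event rate, a 20% 5-year mortality, a 3% withdrawal probability and 3-year recruitment (Trial status). The ranges below run from 4% per year to 20% at 5 years, at a hazard ratio of 0.549. I assume uniform accrual and a 3% loss in total.
- All patients followed until the last one reaches 5 years: about 97 to 107 deaths.
- Each patient followed for 5 years only: about 79 to 87 deaths before withdrawal and 77 to 85 after it.
- First rule, with the 3% read as an annual loss: about 91 to 100 deaths.

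**Clerical line.** 225 × 1.0071 = 226.6, whereas 275 × 1.0071 = 277.0, and half of 550 is 275. The results 277 and 554 are right; only the printed 225 is wrong.

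**The case against.** Three points on the other side carry weight.

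*Origin of 0.52.* A reader might infer from the match with 0.522 that an odds ratio was entered by mistake as a hazard ratio. The article does not show that step. The citation follows the hazard ratio directly and the next sentence speaks of an estimate, so 0.52 could be a model estimate taken from the cited trial, which is not at hand. The match is suggestive and no more. What stands in either case is that the two percentages do not correspond to 0.52 under the model used for the calculation.

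*The assumption is explicit.* A reader might also infer that the stated 80% is an arithmetical error. It is not: the text says it assumes 0.52, and at 0.52 the figure reproduces. A sponsor may choose its target effect. But the article does not present 0.52 as a free choice; its only support is the 19.3% versus 11.1% difference, and for that difference the power is lower.

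*Proportional hazards in the source trial.* The Background section {6a} gives 2-year survival of 88.9% with TEVAR and 95.6% without. TEVAR mortality was thus 11.1% at 2 years and still 11.1% at 5, while medical-arm mortality rose from 4.4% to 19.3%. With such curves a fitted hazard ratio need not equal 0.549. This is a real limit on the conversion, but it does not rescue 0.52 as a reading of the percentages. A rough ratio of deaths to person-time (complete follow-up, deaths spread evenly within 0–2 and 2–5 years) is (0.111/4.556)/(0.193/4.601) = 0.58, further from 0.52. The protocol's own power calculation also assumes a constant hazard ratio, so 0.549 is the conversion consistent with it.

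The step from 0.52 to 0.55 is small beside the uncertainty of a non-significant result from a 140-patient trial. That limits the weight of the point but does not make the sentence correct.

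**Conclusion.** The point holds as a mismatch between the planning value and its stated justification. Under a constant hazard ratio, 19.3% versus 11.1% gives about 0.55 (0.545 to 0.553), not 0.52. The 80% power with 80 deaths is correct at 0.52; for the effect offered in support it is about 74% to 77%, a type II error of 23% to 26% instead of 20%. This rests on proportional hazards, which the source trial's own figures put in doubt.

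Two stronger conclusions are not supported. The documents do not establish that 0.52 was calculated as an odds ratio. Nor do they establish that a higher event target is free: 554 patients reach 93 deaths or fall short of it depending on a follow-up rule that the article does not state. The test, the significance level and the validity of the eventual result are unaffected.

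**What to change.** Choose one of two routes in Sample size {14}, in both the text and the parameter list.

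1. Plan on a hazard ratio of 0.55 and restate the power at 80 deaths as about 75%. If 0.52 is a published model estimate, leave it attributed to the source as such rather than overwriting it.
2. Keep 0.52 as a chosen target effect, or as a cited model estimate if it is one. Delete the statement that it corresponds to the two percentages, and add that power at 0.55 is about 75%.

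Either route costs only wording; the small downside is a less favourable stated power.

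Raising the target to about 88 to 93 deaths is a further option. It needs no extra patients only if everyone is followed until the last patient reaches 5 years, and that rule would have to be written into the protocol. The interim look, set at half the target, would move from 40 to about 44 to 47 deaths.

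In the same edit, change 225 to 275 in the per-arm line; no result changes.

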### Recruitment {15}

With the broad and full participation of all aortic centers that treat uTBAD patients in Nordic countries, the potential for recruitment of subjects is favorable. Involvement of representatives from all five countries in the Trial Steering Committee (TSC) also encourages shared ownership, as has the inclusion of experts from multiple centers in the various discussions regarding the design of the trial.

## Assignment of interventions: allocation

### Sequence generation {16a}

The process of randomization will be carried out by the same third-party electronic dataset system, Research Electronic Data Capture (REDCap), registered at Aarhus University, with 24-h access. Because of the multi-site nature of the trial, randomization will be stratified by the number of clinical sites.

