### Eligibility criteria {10}

#### Inclusion criteria

All subjects, aged 18 or greater at the time of informed consent signature, admitted or referred to the participating cardiovascular Sites with an uTBAD of less than four weeks duration.

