## Statistical methods

### Statistical methods for primary and secondary outcomes {20a}

Both an intention-to-treat and a per-protocol analysis will be performed. As mentioned, in the primary analysis, survival rates will be compared using the log-rank test. Before analysis, log–log-survival versus time plots will be used to visually assess the assumption of proportional hazards supported by statistical tests based on the inclusion of a time-varying covariate for the treatment effect. In the case of crossing survival curves, the overall log-rank test will be reported together with effect estimates in-between crossings. If repeated crossings occur, this will in itself suggest that the intervention does not result in superior outcomes for the subjects, which will then be reported.

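### The primary log-rank test does not use age, which is known for every patient and probably strongly prognostic; adjusting for it is an efficiency gain of uncertain size, not the correction of an error

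*Protocol article*

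**What the plan says.** Four places in the protocol article bear on this.

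- Sequence generation {16a}: "randomization will be stratified by the number of clinical sites". The factor meant is evidently the clinical site.
- Statistical methods for primary and secondary outcomes {20a}: "in the primary analysis, survival rates will be compared using the log-rank test". No strata or covariates are named.
- Sample size {14}: the event count is "based on an overall 1:1 allocation between TEVAR and SMT and analyzed with a log-rank test". The parameter list that closes the section repeats the two-group log-rank test.
- Inclusion criteria: patients are "aged 18 or greater at the time of informed consent signature", with no upper limit, so age is recorded for everyone before randomization.

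Cox regression is named only for exploring subgroups ({20b}). The interim look at 40 events ({21b}) also uses the log-rank test. The article gives no age distribution, no effect of age on mortality and no between-country difference in mortality.

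**The concern.** The endpoint is death from any cause in adults of any age, so age is the obvious baseline predictor. A test that ignores a strong predictor gives up information in two ways. Unmodelled variation in risk pulls the unadjusted hazard ratio toward 1 relative to the ratio among patients of the same age. A chance difference in age between the arms also passes straight into the estimate, and stratifying randomization by site does not prevent it. With only 80 deaths planned and power set near 80%, a few points matter. The data needed are in the database from the day of enrolment.

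**Working it through.** **The plan's own figure.** Inputs from Sample size {14}: "Assuming a true hazard ratio of 0.52 between TEVAR and SMT", two-sided alpha 0.05, power 80%, 1:1 allocation.

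- Freedman: events = ((1 + 0.52)/(1 - 0.52))² × (1.960 + 0.842)² = 78.7, or 79.3 after the 1.0071 interim factor. This rounds up to the stated 80.
- Schoenfeld: 4 × (1.960 + 0.842)² / (ln 0.52)² = 73.4, rounded up to 74.
- Power at 80 events: Φ(√80 × 0.48/1.52 - 1.960) = Φ(0.865) = 80.6% (Freedman); 83.3% (Schoenfeld).

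The planned power therefore holds for an unadjusted log-rank test.

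**Simulation of the alternative.** From the document: 554 patients, 80 deaths, three-year recruitment, 23 sites in five countries, and an "estimated annual event rate of 4% for the primary endpoint in the control group". Assumed: the age effect, site sizes, country shares, permuted blocks of four within site, site and country variation, proportional hazards and no withdrawals. The table holds the hazard ratio among patients of equal age at 0.52, with no site or country variation, 2,000 trials per row.

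| Assumed age HR per SD | Log-rank power | Age-adjusted Cox power | Change (points) |
|---|---|---|---|
| 1.0 | 81.3% | 80.4% | -0.9 |
| 1.3 | 82.6% | 82.6% | 0.0 |
| 1.5 | 81.4% | 82.0% | +0.6 |
| 1.8 | 78.8% | 81.4% | +2.6 |
| 2.0 | 77.7% | 81.0% | +3.3 |
| 2.2 | 77.6% | 82.1% | +4.5 |

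With modest site and country variation (SD 0.2 each on the log-hazard scale), the changes are -0.6, -0.1, +0.8, +1.1, +3.4 and +3.5. The average unadjusted hazard ratio moves from 0.519 at no age effect to 0.536 at 2.2.

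Separate simulations of the same design extend the range. At 1.65 per SD the gain was +1.2 to +1.5. At about 2.2 it was +4.0 to +4.7. At about 2.7 the runs gave +5.8, +6.0 and about +7. The upper end is therefore about 6, give or take simulation error.

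**The other convention.** If 0.52 is read as the unadjusted ratio, the conditional ratio must be stronger. With the unadjusted ratio near 0.50 to 0.52 (4,000 trials each), age adjustment gives:

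- 1.5 per SD: 81.9% to 82.2%, +0.3
- 1.8: 84.4% to 86.4%, +2.0
- 2.0: 82.5% to 85.8%, +3.3
- 2.2: 84.1% to 87.6%, +3.5
- 2.5: 84.2% to 89.2%, +5.0

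**Stratification alone.** Stratifying the log-rank test by country changes power by -0.4 to +0.5 points, and by +0.9 under the largest assumed heterogeneity (SD 0.5 for both site and country). Stratifying by site gives -1.7 to +0.4, and +1.2 in that same case. With 80/23 = 3.5 deaths per site, a usual small loss is expected.

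**Type I error.** With no treatment effect and site-stratified randomization, the plain log-rank test rejected in 5.2%, 3.9% and 4.3% of trials in three settings. The age-adjusted Cox test rejected in 4.9%, 4.1% and 4.2%. The Monte Carlo standard error is √(0.05 × 0.95/4000) = 0.3 points.

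**Chance imbalance.** With an assumed age SD of 12 years and 277 per arm, the standard error of the difference in mean age is 12 × √(2/277) = 1.02 years. About 1 trial in 20 will differ by 2 years or more in one direction or the other. At age hazard ratios of 1.5, 1.95 and 2.3 per decade, a TEVAR arm older by 2 years multiplies the unadjusted ratio by 1.5^0.2 = 1.08, 1.95^0.2 = 1.14 and 2.3^0.2 = 1.18.

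**The case against.** The case for leaving the analysis alone is substantial. The document is consistent: the same test is used for sizing, for the interim look and for the final analysis. A log-rank test is a standard, valid choice for a pragmatic trial. Covariates are often left to a statistical analysis plan, which is not shown and may already include them. The gain depends entirely on an age effect that the document does not give. The event count, the crossing-curve reporting in {20a} and the interim boundary are all tied to the log-rank test, so a change is more than a word.

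Most of this stands, and it limits the point to efficiency. It does not remove it, because the protocol itself names the primary test and sizes the trial on it. An analysis plan that adds age would need the protocol brought into line.

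A reader might infer from {16a} and {20a} that randomizing by site and testing without strata makes the primary test invalid. The null simulations show no inflation of type I error. Nor is that mismatch where the power lies: nearly all the gain comes from age. Country is not a stated randomization factor, and stratifying by it adds no material power.

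**Conclusion.** The stated primary test is sound, with nominal power of about 80%. The protocol passes over a baseline covariate that could add a few points. Across assumed age hazard ratios of 1.0 to 2.7 per SD, adjustment changes power by about -1 to +6 points. The gain reaches 1 point only from about 1.6 to 1.8 per SD. The balance favours adjusting: just under 1 point is lost if age hardly matters, and roughly 4 to 6 are gained if it matters strongly.

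Two stronger readings are not supported. One is that planned power already falls short of 80%. On the document's inputs it is 80.6% or more; the lower simulated figures arise only when a strong age effect is assumed and 0.52 is taken as the age-conditional ratio. The other is that adjustment is free. It needs no new data, but it has the costs given under the fix. The simulated gains are for a Cox model; a covariate-adjusted log-rank test was not simulated.

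**What to change.** - Before the 40-event interim look, prespecify age as a continuous covariate in the primary treatment comparison, or record why this is declined. Use either a Cox model or a covariate-adjusted log-rank test, which keeps the marginal comparison.
- Apply the same test at the interim and final looks, and confirm that the boundary and event target in {21b} and {14} still apply to it. Report the plain log-rank test as supporting.
- Treat country stratification as optional. Stratifying the analysis by 23 sites with 80 deaths is not advised.
- Reword {16a} so that clinical site, not the number of sites, is the stratification factor. This is editorial.

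Cost: amended analysis text and no new data. With a Cox model the reported hazard ratio is conditional on age and depends on the model, and a little power is lost if age proves only weakly prognostic. Adding the covariate after the interim look would be open to challenge, so the timing matters.

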### Concealment mechanism {16b}

As indicated above, randomization or allocation will be performed by REDCap. This electronic dataset is password protected, thus ensuring the concealment of the randomization sequence.

### Implementation {16c}

As noted above, the randomization to either arm will be allocated via REDCap, a process carried out as soon as the acquisition of informed consent is provided in the electronic database.

## Assignment of interventions: blinding

### Who will be blinded {17a}

Due to the nature of one interventional arm of the trial, it is impossible to blind both subjects and investigators to the assignment of treatment. Blinding will be enforced, however, for the analysis of data.

### Procedure for unblinding if needed {17b}

The design is open-label, while data analysis is blinded, so unblinding is not deemed necessary and will not occur.

## Data collection and management

### Plans for assessment and collection of outcomes {18a}

Site initiation prior to approval for subject enrolment includes instructions on data collection and registration in REDCap. Each site has a primary investigator, who is responsible for either registering the data or delegating this responsibility to an approved research assistant. A Trial Management File is kept at each participating site, in addition to a Trial Management File for the entire study group.

### Plans to promote participant retention and complete follow-up {18b}

The typical course of uTBAD requires long, and typically, life-long surveillance. The trial is deliberately designed to mirror the typical follow-up protocol for these patients, thus ensuring participant retention.

### Data management {19}

Site initiation includes instruction in data entry and security, of which the site primary investigator is responsible. The Data and Safety Monitoring Committee (DSMC) will further perform evaluation of the database for data completion and biannual validation of recorded data. The instructions, delegation, and responsibility for these tasks are recorded in each Trial Managers Files and Data Source Manuals.

